## Abstract

**Background:**

Education can create better opportunities for health, and vice versa. Using a so-called ‘add-in’ approach, school-based physical activity (PA) promotion and prevention of sedentary behaviours can increase pupils’ wellbeing and learning and, on the longer term, reduce the risk of non-communicable diseases. A PA ‘add-in’ approach involves integrating PA into teachers’ curricular obligations without being an extra burden as opposed to an ‘add-on’ approach which requires additional operational resources and include activities that do not explicitly contribute towards curricular targets making them less long-term acceptable in a school-based context.

Previous studies investigating education outside the classroom (EOtC) show mutual benefits for both health and education outcomes among children and adolescents. However, the evidence is of mixed quality and questionable certainty, which calls for further investigation. The aim of this study protocol is to describe and discuss the study design and methods to investigate the efficacy and mechanisms of EOtC as a vehicle for health and education. The study investigates the intervention developed and conducted in the TEACHOUT study with updated and strengthened design and measures.

**Methods:**

The efficacy of EOtC will be investigated in a cluster randomised waitlist design. Participants will be pupils in ~54 classes, grades 4-10 (ages 10-15 years) in ~30 Danish elementary schools. Fifteen schools will be randomised to the intervention: a two-day EOtC training course targeting teachers followed by the teachers implementing EOtC >5 hours weekly over the course of one school year. Pre- and post-measures of health (PA and wellbeing) and learning (school motivation and academic achievement) will be collected. Investigation of pedagogical and motivational mechanisms will be based on observations of EOtC.

**Discussion:**

The updated randomised controlled design will provide firmer evidence for the efficacy and mechanisms of EOtC and provide knowledge about how mutual benefits of health and education can be obtained.

**Trial registration:**

Registered with ClinicalTrials.gov (ID NCT05237674) [University of Copenhagen. MOVEOUT: a Cluster RCT of the Efficacy, Mechanisms, and Mediation of an Education Outside the Classroom Intervention on Adolescents’ Physical Activity, 2023], February 14, 2022. Most recently updated on November 23, 2022 (Version 2).

**Supplementary Information:**

The online version contains supplementary material available at 10.1186/s12889-023-16618-3.

## Background

Health and education are synergistic in multifarious ways. Good health supports wellbeing and the cognitive functions underlying learning over the life course [1]. Vice versa, poor health can interfere negatively with schooling, and informal learning in general, through recurrent absences or difficulties concentrating [2, 3]. Good opportunities for learning, on the other hand, provides the basis for participation and informed lifestyles choices. If either education or health is hampered in early life, this will have incremental impacts for both over the life course. Negative feedback loops in childhood tend to track into in adulthood where individuals with higher education generally have higher earnings (and in extension opportunities for healthier foods and living conditions), are more likely to be employed, and to take up positions with fewer risks and physical strains than individuals with lower levels of education [4]. The interconnectedness of health and education calls for coordinated solutions for which efficient and sustainable early-life interventions that can support both health and education in tandem are a necessity. Health and education synergies can be maximised through intersectoral actions, but these actions require a sensitivity towards the core goals, processes, and mandates of the settings through which the actions are implemented. In this protocol, we outline one such approach and describe the methods planned to investigate the efficacy and mechanism of an intervention.

Schools are considered key settings for promoting children and adolescents’ health and education, as they spend a large amount of their waking hours at school [5, 6], and because children and adolescents from all socioeconomic and cultural backgrounds can be reached [5]. However, school-based intervention requires an integration of the associated activities within the core goals, processes, and mandates of schools for successful and sustainable implementation [7]. This is particularly pertinent given the current education milieu in which schools and teachers face external top-down pressures to improve academic standards and improve wellbeing among pupils [8]. This means that there is a need for teaching activities and learning experiences that simultaneously improve pupils’ learning, wellbeing, and health.

Increased physical activity (PA) and decreased sedentary time reduces the risk of non-communicable diseases, such as cardiovascular diseases, diabetes, and morbidity over time [9]. Positive effects are also seen on wellbeing, cognitive functioning [10], and academic achievement during childhood [11]. European adolescents are far from reaching the PA guidelines, and activity levels decline with increasing age [12]. Furthermore, the decreasing levels of wellbeing and rise of mental health problems among adolescents has increased during the recent years [13]. Various attempts have been made to increase PA during school hours, e.g., through extracurricular activities such as active brain breaks or time slots allocated for movement activities [14, 15]. However, these approaches are often disconnected from school objectives, require additional manpower, or increasing workload for existing personnel and is not considered a primary objective by the teachers, which in many cases cause a low degree of implementation [16]. In contrast, ‘add-in’ approaches that integrate PA within primary pedagogical and didactical purposes have shown to achieve better adherence [7]. Education outside the classroom (EOtC) is be such an approach [17, 18].

EOtC has received widespread attention in the face of COVID-19 as a means to reduce school-based transmission [19]. Recent evidence suggests that EOtC in general, and perhaps even more so when conducted in nature, holds benefits for health and wellbeing [20–22]. Pupils have been observed to engage in more PA during EOtC compared to usual classroom-based teaching [23–25] as well as report higher school wellbeing [26, 27], school motivation [28], and academic achievement [29]. Therefore EOtC has been characterised [17, 18] as an intersectoral [30] and integrated ‘win-win’ opportunity for both health and education sectors, i.e., an ‘add-in’ approach to school-based PA promotion [7].

In EOtC, teaching sessions are relocated from the classroom to, for example, public open spaces, societal institutions, or outdoor spaces on school property. Examples include the use of the properties in the local neighbourhood to teach geometry (e.g., identifying square or triangular objects), writing poems in and about the city, investigating local history in the neighbourhood, doing STEM education at science centers, or learning about biological and chemical processes through school gardening [31]. The aim of EOtC is to promote learning and wellbeing through practical exercises and the use of one’s body and senses in authentic situations [32, 33]. EOtC often involves teaching activities that require active transportation to and around places outside the school buildings. EOtC is further characterised by the pedagogical and didactical elements of pupil-led approaches, collaborative, action-centred, experiential, inquiry-based and thematic, play-based learning processes, and movement [34, 35]. EOtC involves outdoor teaching explicitly aligned with and contributing to teachers’ obligations [17, 21, 34], often in a cross-curricular approach.

The pedagogical approaches that underpin EOtC are thought to stimulate investigative behaviours based on pupils’ curiosities alone or in groups, and thereby foster experiences with autonomy as well as relatedness. Tangible and practical work allows an experience of being competent in other fields than, e.g., reading and writing. EOtC pedagogy thus aligns with Self-Determination Theory’s (SDT) [36, 37] perspective on motivation and wellbeing [36] in enabling experiences of autonomy and a sense of competency in close relations with teachers and peers [38–40]. SDT is one of the leading wellbeing and motivation theories in the world and widely used in the context of education [41, 42]. SDT represents a broad framework for the study of human motivation, flourishing, and wellbeing. At the centre of the theory is the individual’s basic psychological need for *autonomy, competence*, and *relatedness*, which when fulfilled has been shown to result in wellbeing and the most self-determined forms of motivation [43–45]. SDT’s usefulness for EOtC interventions was confirmed in the so-called TEACHOUT study [28, 38] and has also been used as a central theory to explain the benefits of EOtC in other studies [46, 47].

The TEACHOUT study was conducted in the school year 2014–2015 [38]. The study was a quasi-experimental investigation of the associations of EOtC with PA, wellbeing, and learning among pupils in grades 3-6in Danish public schools. The study was the first large-scale quantitative multi-outcome investigation of EOtC, and a trailblazer study in its field [21, 48]. The TEACHOUT intervention included a two-day training course for teachers followed by them implementing EOtC at least five hours a week, divided in 1–2 weekly sessions, for one school year [49]. The study showed that regular practice of EOtC was positively associated with device-based measured PA, with the boys seeming to accrue more moderate-to-vigorous PA (MVPA) and girls more light PA (LPA) [23, 24]. The TEACHOUT study also showed positive effects on pro-social behaviour [26] and in-class social relations [27], motivation for school [28], and reading competence [29]. However, this previous research on effects of EOtC has methodological limitations that need to be addressed. PA was only measured once during the intervention, making the design of the PA evaluation cross-sectional and unable to exclude influences of extraneous impacts on outcomes. This made it impossible to ascertain whether it was EOtC itself that lead to improvements in PA over and above the usual practices in the schools. In addition, the study sample did not allow for investigation of subsamples of pupils, e.g., pupils with overweight or inactive girls, who might attain different benefits of EOtC. Furthermore, the collected data did not allow for investigation of compensatory movement behaviours outside the school day [50] or potential adverse effects (e.g., subgroups who do not feel comfortable or safe outside). Furthermore, there is a need for investigation of which pedagogical and didactical elements of the EOtC that mediate and moderate potential effects.

Therefore, on the foundation of both the merits and limitations of the original TEACHOUT study, this study protocol describes the MOVEOUT study. The MOVEOUT study will provide a more robust and reliable evaluation of the potentials and mechanisms of EOtC. Evidence from MOVEOUT will allow formulation of guidelines for practice and policy with details about the pedagogical and didactical elements of EOtC, which need to be emphasised in the ongoing expansion of EOtC.

### Aims

This study protocol outlines the design and methods of the MOVEOUT study. The objectives of the MOVEOUT study are to investigate the efficacy and mechanisms of the *TEACHOUT intervention* [49] (hereafter, the intervention) on Danish grade 4–10 pupils’ (aged 10–16 years) school-based and overall PA behaviours, school motivation, wellbeing, and academic achievement over the course of one school year in comparison to the schools’ usual practice. The schools’ usual practice typically involves indoor classroom-based activities. The intervention is the same well-described and manualised EOtC intervention that was investigated in the abovementioned quasi-experimental study, TEACHOUT [49]. See the MOVEOUT study Theory of Change, Fig. 1.

**Fig. 1 Fig1:**
[figure not shown]
The MOVEOUT study theory of change

### Sub-studies and hypotheses

The study objectives will be reached through two sub-studies – an efficacy and a mechanism study – testing six main hypotheses, which are illustrated in Figure 2.

**Fig. 2 Fig2:**
[figure not shown]
Illustrations of the hypotheses of the two sub-studies

#### Sub-study 1

Effects of EOtC (see full pre-registered protocol for H1 and H2 ([51]).

H1 Pupils in the intervention group will retain higher PA intensities compared to the control group, specifically a) more MVPA, b) more LPA, and c) less SED time (referred to in the following only as PA intensities).H2 Pupils in the intervention group will retain a) more running, b) more walking, c) more standing, and d) less sitting time compared to the control group.H3 Pupils in the intervention group will achieve higher school motivation, wellbeing, and academic achievement compared to the control group.

#### Sub-study 2

Mechanisms of EOtC. The unit of analysis is schooldays or sessions.

H4 EOtC schooldays or sessions will be associated with higher PA intensities, higher levels of intrinsic motivation, and more positive perceptions of the teaching environment compared to usual schooldays or sessions.H5 The pedagogical and didactical elements during EOtC sessions will be different from the pedagogical and didactical elements during usual sessions.H6 The expected association between EOtC and PA intensities, intrinsic motivation, and perceptions of the teaching environment will be mediated by the pedagogical and didactical elements of the EOtC sessions.

## Methods

The following paragraphs outlines the methods of the MOVEOUT study in accordance with the SPIRIT (Standard Protocol Items: Recommendations for Interventional Trials) guidelines [52]. Recruitment, data collection, and intervention training was commenced prior to publication of the protocol (but after registration to ClinicalTrials), and parts of the sections pertaining to past events are therefore written in past tense below.

The MOVEOUT study is a cluster-randomised trial with randomisation occurring at school level. Elementary schools with one or more classes enrolled was randomly assigned to the intervention or control groups. The intervention consisted of a two-day training course on EOtC given to schoolteachers followed by the teachers applying EOtC for at least five hours a week with their class, in 1–2 weekly sessions for one school year. The training course was supplemented by two one-hour inspirational webinars during the first half of the school year (see TIDieR checklist for more detailed description [49]). The schools assigned to the control group will continue their teaching as usual for one school year upon which they will also receive the intervention. See timeline of enrolment, allocation, intervention, and data collection according to SPIRIT in Table 1 and Fig. 3.

**Table 1 Tab1:** Participant timeline according to SPIRIT

	STUDY PERIOD							
					Implementation			
	Enrolment	Pre-test A	Pre-test B	Allocation		Post-test A	Post-test B	Close-out
Time point	-18 mo.	-2 mo.	-1 mo.	0 mo.	4 mo.	10 mo.	11 mo.	14 mo.
**ENROLMENT**	x							
Eligibility screen	x							
Informed consent	x							
Allocation (cluster)				x				
**INTERVENTIONS**								
Two-day training course				x				
Two one-hour inspirational webinars					x			
Applying EOtC > five hours pr. week in 1–2 weekly sessions					x	x	x	x
**MEASUREMENTS**								
* Participants*								
Pupil socioeconomic status (parent survey)	x							
Pupil health status (parent survey)	x							
Implementer descriptives (teacher survey)	x							
* Pre- and post-measures*								
PA behaviours (pupil device based, seven days)		x	x			x	x	
School motivation (pupil questionnaire)			x				x	
Wellbeing (pupil questionnaire)			x				x	
Academic achievement (pupil tests)			x				x	
* School days/sessions measures (two EOtC and two non-EOtC schooldays, IG only)*								
PA behaviours (pupil device based, session)					x			
School motivation (pupil survey, school day)					x			
Learning environment (pupil survey, school day)					x			
Didactical and pedagogical elements (observation, school day)					x			
* Implementation*								
Degree and characteristics of the EOtC (teacher questionnaire, weekly)					x	x	x	x
Adaption, acceptability, and local supportive structures (teacher interview, IG only)						x		
* Background descriptive measures*								
Socioeconomic status (survey, parent/legal guardian)		x						
Child health status (survey, parent/legal guardian)		x						
Teacher’s previous work and EOtC experience (survey)			x					

*EOtC *Education outside the classroom, *IG *Intervention group. *Mo *Month(s), *PA *Physical activity

**Fig. 3 Fig3:**
[figure not shown]
Participation allocation flowchart of the MOVEOUT study according to SPIRIT

### Setting and context

The study is conducted in Denmark in typical Danish elementary schools (for 6- to 16-year-old children). Regular practice of EOtC has increased markedly in Denmark within the last twenty years with at least 19.5% of all schools reporting EOtC in some of their classes in 2019 [53].

During the COVID-pandemic, Denmark was among the first European countries to reopen schools by allowing teaching in primary school classes to take place outdoors [54]. This fostered a further boom in schools and teachers seeking supportive guidelines for outdoor classroom management and ideas of EOtC [55]. In response, various educational actors and organisations developed and offered the needed knowledge, extending the general supply of freely available materials, e.g., Children & Nature – Denmark [56].

### Recruitment and participants

We aimed to recruit ~ 54 classes (~ 81 teachers) from 30 Danish general (non-special need) education elementary schools; on average 1.8 classes per school, 1–2 teachers and 21 pupils per class, with a total of 1.134 pupils aged 10–16 years (see Fig. 3). Pupils with noteworthy health problems, reported by their parents or legal guardian, teachers, or investigators will be excluded from the analyses.

Schools in municipalities with larger proportions of citizens with lower levels of education than the average for the region were strategically invited for enrolment in the study. Schools located in the Capital Region and Region Zealand were invited to begin with. Thereafter, schools in Region of Southern Denmark were invited, and finally invitations were distributed nationally via teacher networks. School classes were not allowed to be involved in other school development or research projects.

Recruitment and enrolment started around two years before the implementation of the intervention and continued until randomisation (month − 18 to 0, see Table 1). Teachers were recruited via both municipal school directors and direct contact to local school principals. Municipalities and schools were initially contacted via e-mail and non-responders were then contacted via telephone. Online information meetings were held with school principals and teachers. Participating teachers informed the parents and were provided with written material available in Danish and English, and supplementary video material introducing the study (see Supplementary Information, Additional files 1, 3, and 4). Parents were given a letter with additional information about the study’s rationales and background, and an analogue consent form. The recruitment process was supported by general information on the MOVEOUT study project website (www.moveoutstudy.dk) [57].

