### Randomisation

Randomisation was performed by PE and MB on 1st of April 2022 (Month 0, see Fig. 4), and was made public on YouTube (see Supplementary Information, Additional file 1). Immediately after, the enrolled schools and teachers were informed by e-mail about the result of the randomisation process.

To ensure a balanced representation of grade levels across the intervention and control groups, stratified block randomisation in a 1:1 ratio was used (i.e., schools with participating classes in grade 4–6 and schools with classes 7–10 were randomised block wise in RStudio using the ‘dplyr’ and ‘readxl’ packages).

Due to the type of the intervention, it was not possible to blind the participants to group allocation. However, allocation levels will be coded before analyses and the analysts will not be informed about the codes before the final analyses have been performed.

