#### Statistical analyses

Estimation of intervention effects (H1, H2, and H3 of Sub-study 1) will be computed using a ‘per-protocol’ analysis [67]. All classes in the intervention group not adhering to the classification of ‘regular EOtC’ (an average of > 150 min of weekly EOtC over the school year) and all classes in control group practicing too high amount of EOtC (average of > 150 min of weekly EOtC over the school year) will be excluded. These analyses will be complemented with sensitivity analyses, following the principle of ‘intention-to-treat’ [67] which will include all schools in the analyses irrespective of their adherence to the intervention or control condition.

Linear mixed models (LMM) will be used to analyse how post-test scores varies as a function of whether the pupils were assigned to the intervention or the control group while taking into account pre-test scores, sex, age, and random effects of classes and schools. Please, see the H1 and H2 pre-registration for further information on the pre-processing steps and statistical modelling used for these data [51]. The base model used to assess H3 (effects on school motivation, wellbeing, and academic achievement) will include baseline as a covariate and school and class ID as random factor, and group allocation as the fixed effect of primary interest. Follow-up stepwise modelling will be used to investigate the contribution of previously shown confounders, i.e. primarily the number of weekly EOtC sessions [26], age, and sex [23, 68, 69], to the base models. All sub-studies will be reported following the CONSORT statements and flowchart [70].

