### Background descriptive measures

Perceived child health status and data on socioeconomic status (parents’ or legal guardian’s education level and occupational status) will be collected using the Danish Occupational Social Class Measurement [82] with the pupils’ parents (or legal guardian) (Month -2, see Table 1).

Quantitative data about teachers previous work experience and previous experience with their use of EOtC will be collected from the intervention and control group teachers (Month 0, see Table 1).

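### Sub-study 1 allows pupils to be excluded after randomisation for undefined health problems reported by people who know the allocation, and the intention-to-treat analysis does not say it keeps them

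*Protocol article*

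**What the plan says.** Protocol article, Recruitment and participants: "Pupils with noteworthy health problems, reported by their parents or legal guardian, teachers, or investigators will be excluded from the analyses". The rule names three kinds of reporter and removes pupils from the analyses without naming an analysis set. It gives no criteria and no date.

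Randomisation (performed on 1 April 2022, Month 0): "Due to the type of the intervention, it was not possible to blind the participants to group allocation". Straight afterwards, "the enrolled schools and teachers were informed by e-mail about the result of the randomisation process", and the procedure itself "was made public on YouTube". The one safeguard is on the analysis side: "allocation levels will be coded before analyses and the analysts will not be informed about the codes" until the final analyses are done.

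Sub-study 1, Statistical analyses: the main analysis is per-protocol, dropping classes by their average weekly EOtC minutes. An intention-to-treat sensitivity analysis accompanies it, "which will include all schools in the analyses irrespective of their adherence to the intervention or control condition".

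Background descriptive measures: "Perceived child health status and data on socioeconomic status" come from parents or guardians at Month -2. Table 1 marks the parent health survey at enrolment and again at Pre-test A, both before allocation. It lists no teacher or investigator health report.

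**The concern.** A health exclusion is harmless to a randomised comparison if it is settled before allocation, because it then only narrows the population. It stops being harmless if it can be triggered later by someone who knows the arm, because the two groups being compared may then be selected differently.

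The rule leaves that route open. Teachers deliver or withhold the intervention and know which they are doing, and nothing dates their reports. The criterion is also close to what is being measured. Physical activity is the outcome for H1 and H2, and KIDSCREEN-27, a health-related quality-of-life instrument, is an outcome for H3. Pupils removed for health reasons may well differ from their classmates on both.

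At stake is whether any planned between-arm analysis contains the pupils as randomised. The per-protocol analysis already departs from that by class, so the intention-to-treat analysis is the only one that could provide it.

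**Working it through.** **1. Who may report, when, and with what knowledge of allocation.**

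| Source | Dated report in the article | Knows allocation? |
|---|---|---|
| Parent or guardian | Survey at enrolment / Month -2, before randomisation | Not at that time |
| Teacher | None | Yes, informed by e-mail |
| Investigator | None | Probably; inferred from the published randomisation |
| Analyst | Not a reporter | Coded allocation |

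Coding the allocation guards against selection by analysts. It does not reach the people whose reports trigger an exclusion.

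**2. Which analysis restores the pupils.** The intention-to-treat analysis is defined by schools and by adherence. It reverses the class-level per-protocol exclusions. A pupil removed for health was not removed for adherence, so the wording neither keeps nor drops that pupil.

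**3. Scope.** Sub-study 2 compares EOtC with usual school days within intervention-group pupils only. An exclusion that differs by arm cannot arise there, so the point concerns sub-study 1.

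**4. Reference figure.** The Sample size section gives a detectable d of 0.374 [0.187, 0.561] at 95% power, one-tailed. For three levels with schools randomised 1:1:

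MDES = (t[0.95, K-2] + t[0.95, K-2]) × sqrt(4 × [ICC_school/K + ICC_class/(JK) + (1 - ICC_school - ICC_class)/(JKn)])

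With K = 30 schools, J = 1.8 classes per school, n = 17 pupils per class, and ICCs of 0.035 (school) and 0.046 (class):

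- SE = sqrt(4 × [0.035/30 + 0.046/54 + 0.919/918]) = 0.1099
- MDES = 3.402 × 0.1099 = 0.374, interval 0.187 to 0.561

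The plan's figure is reproduced. With the stated 51 classes (J = 1.7) it is 0.381. The figure serves here only as a yardstick.

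**5. Illustration of bias.** The article gives no health-exclusion rate; the 20% allowance in Sample size names only drop-out and invalid accelerometer data. All rates and deficits below are therefore assumptions. If a share f of an arm is removed and those pupils average δ SD below that arm's mean, the mean of the remainder rises by fδ/(1 - f). The between-arm shift is the difference of two such terms:

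- 6% against 3%, δ = 1: 0.06/0.94 - 0.03/0.97 = 0.0638 - 0.0309 = 0.033
- 8% against 3%, δ = 1: 0.08/0.92 - 0.03/0.97 = 0.0870 - 0.0309 = 0.056

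**6. Baseline adjustment.** The planned models adjust for the pre-test score. If the deficit is equal at pre- and post-test and the pre-post slope is b, about (1 - b) of the shift remains. No slope is given; b = 0.5 to 0.7 is assumed, which leaves 0.5 to 0.3 of it.

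| Exclusion rates (one arm v other) | Unadjusted shift in SD, δ = 0.5 | Unadjusted shift in SD, δ = 1.0 | Adjusted range in SD |
|---|---|---|---|
| 1% v 0% | 0.005 | 0.010 | 0.002–0.005 |
| 6% v 3% | 0.016 | 0.033 | 0.005–0.016 |
| 8% v 3% | 0.028 | 0.056 | 0.008–0.028 |
| 10% v 0% | 0.056 | 0.111 | 0.017–0.056 |

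The adjusted column applies only to stable conditions. A problem that arises after the pre-test is not captured by the pre-test score, and the unadjusted columns are then the closer guide. The shift favours whichever arm loses more low-scoring pupils.

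**7. Precision.** Removing 10% of pupils evenly moves the detectable effect from 0.381 to 0.388. The issue is bias, not power.

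**The case against.** The strongest reply is that this is a condensed article. A definition and a date may stand in the pre-registration it cites, and the sentence sits in a recruitment section, beside the target population, with an eligibility screen at enrolment in Table 1. Read that way, the exclusion is an entry criterion applied before allocation. This is a fair reading, but the text does not secure it. The rule removes pupils from the analyses, not from enrolment. The pre-registration is cited for H1 and H2 only, and not for this rule. Nothing prevents a later report. The flaw also lies in what is stated (who may trigger removal, and from what), not only in a missing definition.

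Several stronger readings are tempting and should be resisted:

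- A reader might infer that the bias favours EOtC, because intervention teachers are outdoors with pupils every week and the session observations and teacher interviews take place in that arm only. This shows unequal study contact. It does not show unequal reporting: control teachers also see their pupils all year, and no reporting procedure that differs by arm is described.
- A reader might take investigators to be unblinded as a stated fact. The article does not say so; it is an inference from the published randomisation.
- A reader might conclude that the intention-to-treat analysis definitely applies the health exclusion. It is silent on the matter.
- A reader might quote 0.056/0.374 = 15% of the detectable effect as the size. That uses an assumed 8% against 3% split, the larger assumed deficit and no baseline adjustment.

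**Conclusion.** The point holds for sub-study 1, and it should be acted on. As written, the rule permits outcome-related exclusion of pupils after randomisation, on reports from teachers who know the arm and investigators who probably do. No planned between-arm analysis is stated to be free of it. The document shows the opportunity for bias, not its occurrence, and neither direction nor size can be derived from it.

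On the assumed rates of 6% or 8% against 3%, the adjusted shift is at most a few hundredths of an SD (0.005 to 0.028, or about 1% to 8% of 0.374). Only the extreme assumption of 10% lost from one arm and none from the other brings the adjusted figure to 0.056. These values rest on assumed rates, assumed deficits and an assumed pre-post slope, and for conditions arising after the pre-test the reduction does not apply. The case for change rests less on magnitude than on protecting the randomised comparison at almost no cost.

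**What to change.** Amend the analysis wording for sub-study 1:

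- Limit the health exclusion to conditions specified in advance and recorded before randomisation, in the parent survey at enrolment or Month -2.
- Do not exclude pupils on teacher or investigator reports made after 1 April 2022.
- Keep all randomised pupils with outcome data in the intention-to-treat analysis, and apply the health exclusion there only as a sensitivity analysis.
- Report the number of health exclusions by arm, with the source and date of each report.

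No new data are needed, because the parent survey is already scheduled. The downside is slightly more outcome variance from keeping a few pupils with health problems. The parent survey records perceived health and may miss some conditions; those pupils would then stay in, which does not disturb the comparison between arms.
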